### Dependent variables

**Reaction**: assessment of satisfaction with the intervention. Satisfaction will be measured with a qualitative survey on the formative activity that will be administered to the intervention groups after playing the game (Table 3).
**Learning **

**Table 3 Tab3:** Satisfaction survey

**Question**	Answer
Level of satisfaction with the activity	Likert 1–5
The format of the activity allows learning to be achieved	Likert 1–5
Satisfaction with the downloadable materials	Likert 1–5
Do you think it will change your attitude towards addressing sexuality/STIs?	Likert 1–5
Positive aspects to highlight	Open
Negative aspects or suggestions	Open

Knowledge change will be measured with a self-developed questionnaire. Prior to implementation, the questionnaire will be validated through evaluation by a group of health professionals with expertise in STIs and pilot testing by resident doctors and nurses who will not subsequently participate in the study. The clarity of the questions, comprehension of the instructions, length of the test, and relevance of the distractors will be evaluated. Modifications suggested in the expert judgement and pilot testing will be incorporated into the questionnaire.

The questionnaires will include:

Knowledge test (Table 4): 25 multiple choice questions with 4 possible answers.

**Table 4 Tab4:** Knowledge test

Area	Questions
Prevention and detection of gender violence	1, 2, 3, 4, 5
Emergency contraception and abortion	6, 7
Anamnesis	8
Screening and diagnosis	9, 10, 11
Transmission	12, 13, 14
STI approach and treatment	15, 16, 17, 18, 19, 20, 21, 22, 23, 24, 25
Extra question – no points	26

The items included in the questionnaire will be prevention of gender violence and/or violence based on sexual identity or orientation and clinical approach to STI.3.Evaluation of changes in the application of the knowledge acquired in clinical practice

The impact of the training intervention will be evaluated for 6 months by studying different variables related to the clinical approach to treating STIs:Performance of diagnostic tests: multitest PCR, exudate culture, and serology.Recording of aetiologically oriented health problems in clinical history.Number of epidemiological surveys (data provided by the Public Health Agency).Prescription of antibiotics.

These clinical data will be collected from health professionals during the 6 months following the intervention, both in the intervention and control groups.

Antibiotic use data will be collected from electronic prescriptions generated by health professionals.

## Data collection and sources of information

The participants in each group will complete an initial knowledge test. Once the first knowledge test will be completed, the participants in the intervention group will carry out the training activity, and at the end of the activity, they will answer the knowledge test again and complete a satisfaction survey on the same platform. The control group will not complete these post-intervention questionnaires. After 3 months, the knowledge test will be repeated for both the intervention and control groups. The data will be collected and stored in the same way.

Clinical data (request for tests, recording of health problems and antibiotic prescriptions) will be extracted from the computerized medical records.

Data from epidemiological surveys of notifiable diseases will be requested from the Public Health Agency.

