## Methods

We will design, develop, and evaluate an educational intervention in the form of a video game aimed at primary care professionals. The intervention will be studied and compared with control groups that will not carry out the intervention.

Design: Design-cluster randomized clinical trial with pre-post evaluation. The PCC teams (health professionals working in a primary care centre (doctors, nurses and residents)) will be randomly assigned to the intervention or control group.

The intervention groups are doing a preintervention test, which will be repeated immediately after the intervention and then 3 months later. In the control groups, the test will be administered at the beginning of the study and repeated after 3 months. In addition to questions to assess knowledge, there will be a qualitative assessment satisfaction survey for the participants. This test will also be carried out at the same time in control groups with the same sociodemographic characteristics.

The intervention will consist of an online video game developed by a multidisciplinary team.

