## Study population, site participation, and recruitment

The study will be conducted in primary care centres (PCCs) managed by the Institut Català de la Salut (ICS, Catalan Health Institute), the main primary care service provider in Catalonia, with the participation of family and community medicine areas and nursing residents and professionals from PCCs of the public health system.

The study will start on April 2024 (Timeline in Table 1).

**Table 1 Tab1:** Timeline

Task	Date
Questionnaires design and piloting	2023
Recruitment of PCC	January—May 2024
Training Intervention	May–June 2024
Data collection from questionnaires	May – October
Clinical data collection	May – December

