### Recruitment of participants

The PCCs (Table 2) will be invited to participate in the study by training referents. Participation in the study will be proposed by the primary care training referral platform. A letter and a slide presentation will be made to explain the study. Once the PCCs who wish to participate have been selected, they will be randomly assigned to a control/intervention group (Fig. 2).

**Table 2 Tab2:** PCC invited to participate in the study

Territorial management of primary care	Primary care center
Barcelona	CAP Adrià
	CAP Besòs
	CAP Bon Pastor
	CAP Bordeta-Magòria
	CAP Casc Antic*
	CAP Casernes
	CAP Chafarinas
	CAP Ciutat Meridiana
	CAP Doctor Carles Ribas
	CAP Doctor Lluís Sayé*
	CAP Drassanes*
	CAP El Carmel
	CAP El Clot*
	CAP Encants*
	CAP Gòtic*
	CAP Guinardó
	CAP Guineueta
	CAP Horta
	CAP La Marina
	CAP La Mina
	CAP La Pau*
	CAP La Sagrera
	CAP Les Indianes
	CAP Manso
	CAP Montcada i Reixac*
	CAP Montnegre
	CAP Numància
	CAP Pare Claret
	CAP Passeig de Sant Joan*
	CAP Poblenou
	CAP Ramon Turró
	CAP Rio de Janeiro
	CAP Roger
	CAP Roquetes-Canteres
	CAP Sanllehy
	CAP Sant Andreu
	CAP Sant Martí de Provençals
	CAP Sant Rafael
	CAP Sants
	CAP Trinitat Vella
	CAP Turó
	CAP Vila de Gràcia-Cibeles
Catalunya Central	CAP Navàs Balsareny*
	CAP Sant Joan de Vilatorrada*
Metropolitana Nord	CAP Mollet del Vallès Oest*
Metropolitana Sud	CAP Vilavella (St Vicenç dels Horts—Torrelles) *

Centres marked with an asterisk are already enrolled

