### Assignment of intervention/control groups

The assignment will be randomized by clusters (PCC).

Once the centres have been recruited, they will be stratified and matched according to the following variables: teaching/nonteaching status, classification according to the MEDEA index, percentage of assigned population of migrant origin and number of family doctors and primary care nurses with assigned quotas.

Centres with similar characteristics will be randomly assigned to the control or intervention group. The allocation of PCCs to each group will be made by a person outside the circle of researchers using a table of random numbers.

The individuals in the control group will be able to carry out the training activity once the study will be completed.

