### Study population

*Inclusion criteria for participants* will be as follows: family and community medicine and nursing residents; family doctors; and primary care nurses with assigned quotas.

*Exclusion criteria* will be: not having online gaming devices; not being able to follow up for 6 months; being an STI referral professional (STI referrers are those professionals who, after specific training, are designated as consultants with or without their own STI agenda).

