### Limitations

The intervention to be assessed cannot be masked since it could influence its effect. Because there is a possibility of contamination bias among professionals, randomization by clusters is proposed under the assumption that the number of clusters would be sufficient for each group.

Geographic dispersion of the PCC will reduce the possibility of contamination.

Participants will know they are being assessed, which could lead to observer bias, although comparisons with a control group who will also know they are being observed may reduce the effect of this bias in the surveys. On the other hand, regarding the clinical variables of the professionals, it is thought that the observation time is long enough that the fact that they are being observed does not interfere with their clinical use.

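### As written, centres are randomised before individual professionals are enrolled or tested, so who takes part and their baseline scores may depend on the centre's allocation

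*Protocol article*

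**What the plan says.** The protocol article gives the order of events in several places.

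- **Recruitment of participants:** the training referents invite centres. "Once the PCCs who wish to participate have been selected, they will be randomly assigned to a control/intervention group".
- **Assignment of intervention/control groups:** "Once the centres have been recruited, they will be stratified and matched according to the following variables". The variables are all centre characteristics. A person outside the research team makes the allocation from a random number table. Control professionals may do the training when the study is over.
- **Methods:** "The intervention groups are doing a preintervention test, which will be repeated immediately after the intervention and then 3 months later".
- **Data collection and sources of information:** "The participants in each group will complete an initial knowledge test". The intervention participants then play the game.
- **Table 1:** "Recruitment of PCC January—May 2024", with training and questionnaire collection both starting in May. It has a row for recruiting centres and none for enrolling individuals.
- **Study population:** individual exclusion criteria apply, among them "not having online gaming devices; not being able to follow up for 6 months".
- **Limitations:** "The intervention to be assessed cannot be masked". The section discusses contamination and observer bias, but not selection of individuals within centres.

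**The concern.** In a cluster trial, randomisation makes the centres comparable. It makes the participants comparable only if the people in each centre are identified without regard to the arm. If they are approached, screened or tested after the arm is known, the two arms can attract different people. Here the two offers differ: one arm plays a team game now, the other completes tests and has access to the game later. Interest in sexual health or in games could then influence who joins, and differently by arm.

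The knowledge comparison would mix the effect of the game with differences in who joined. The clinical-record outcomes are exposed too: the article describes these data only for the six months after the intervention, so it mentions no earlier value to adjust for. The baseline knowledge score is the natural covariate, but under this order it is measured in people whose participation, and perhaps effort on the test, may already reflect the allocation. Enlarging the sample would not remove such a bias.

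**Working it through.** No figure in the article bears on this point, so the check sets its statements side by side.

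1. **What is recruited before allocation?** The sections on recruitment and on assignment both name centres. Neither says that individual professionals are listed, consented or tested at that stage.

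2. **When is the baseline test taken?** The Methods section assigns the pretest to the intervention groups, and the data-collection section assigns the initial test to participants in each group. Both describe people who already belong to an arm. Table 1 is compatible with this, since centre recruitment runs from January to May and questionnaires start in May. It is given in whole months, however, and in the intervention arm the test has to come shortly before the game in any case. It is consistent with the order but does not prove it.

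3. **Could the arm be known by then?** The intervention cannot be masked, and controls have deferred access. Once a centre's allocation is disclosed, nothing described in the article keeps it from the professionals working there. The article does not say when disclosure happens.

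4. **Do the stated safeguards cover individuals?**
   - The independent allocator protects the assignment of centres. That person has no bearing on who joins within a centre afterwards.
   - Stratification and matching use teaching status, the MEDEA index, the share of migrant population and staff numbers. These balance centres, not the motivation of the professionals who take part.
   - The planned analysis compares baselines and says that ANCOVA could be useful. Adjustment can deal with measured prior knowledge, at least in part. It cannot be relied on for unmeasured interest or motivation.

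5. **Can the bias be sized?** No. That would need the participation rate by arm and the relation between willingness to join and the outcome. The article gives neither.

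The stated order therefore leaves a route by which allocation can affect participation and baseline scores, and no described safeguard closes it.

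**The case against.** The strongest reply is that the timing of individual enrolment is inferred. To say that participants in each group take a test is an ordinary way of saying that both arms are tested; it fixes neither the date of enrolment nor what people knew. The Methods section randomises teams of professionals, and the section that describes the letter and slide presentation before assignment is headed as recruitment of participants. Professionals may thus have been approached, and may have agreed, before allocation. The article is also a condensed account, and its timeline figure is not shown.

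Much of this stands, and the point is worded conditionally for that reason. It does not remove the point. Wherever the article gives the order, centres are allocated first and the test comes from people in groups, and individual exclusions still apply within the teams. The question is about a stated sequence for which a better one exists.

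Three stronger readings are tempting, and the document does not support them.

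- **That professionals certainly know their arm when they join.** The sentence in the Limitations section concerns masking the intervention. An intervention that cannot be masked can still have its allocation withheld until the baseline test is done.
- **That the device criterion filters only the intervention arm.** The Study population section states it for all participants, and controls may play later.
- **That a particular inflation of the false-positive rate follows.** Any such rate rests entirely on an assumed shift in scores, for which the article gives no basis. The pilot SD of 4.07 describes score improvement, not the residual spread after baseline adjustment.

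Deferred access may also be an incentive for controls to join, so even the direction of any selection is uncertain.

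**Conclusion.** The point holds in conditional form. As the article is written, individual participation and baseline scores may depend on the centre's allocation; randomising and matching centres does not prevent this, and baseline adjustment may not fully remove it. This rests on two assumptions: that individuals are enrolled and tested in the order described, and that the centre's arm has been disclosed by then. If either is wrong, one clarifying sentence settles the matter. The size of any bias is unknown and cannot be derived from the document. This is a cheap improvement to the procedure and not evidence that the trial's result will be biased.

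**What to change.** Re-order the recruitment steps. After a centre consents, and before its allocation is disclosed:

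1. list the eligible professionals and enrol those who agree;
2. apply the exclusion criteria from the Study population section;
3. administer the baseline knowledge test.

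Then disclose the allocation, and analyse everyone enrolled at that point in their centre's arm. If this is already the practice, say so in the recruitment section.

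For any centre whose allocation has already been disclosed, report the numbers eligible, invited and participating, by arm and centre, so that readers can judge whether participation differed.

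The change needs no extra participants and no new instrument. The baseline test opens somewhat earlier, and the price is a longer gap between it and the training.

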**Methods/design:**

Multicentre cluster randomized controlled trial.

Groups of primary care professionals will receive an intervention (online video game on sex education and STIs [SEXIT]) and will be compared with control groups that will not receive the intervention. Group assignments will be randomized by clusters.

The study will consist of a pre-post evaluation of the intervention: a knowledge test will be administered before and after the intervention and 3 months after the intervention. This test will also be carried out on the same time sequence in the control groups. The impact of the training intervention will be assessed over a 6-month period, focusing on various variables associated with the clinical management of STIs. This evaluation entails the clinical records of diagnostic tests and antibiotic prescriptions related to the clinical approach to STIs.

The required sample size is 262 (131 per group).

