### Planned analysis

For the treatment and analysis of the data, a descriptive analysis of the variables (percentages and averages with measures of dispersion) will be carried out according to the nature of the variables.Demographic and background data: descriptive statistics will be used (mean, median, standard deviation, range) to summarize the characteristics of the participants, including age, sex, years worked, etc. The distribution of test scores will be used to observe the distribution of pre- and postintervention test scores.Sensitivity analysis of the instrument: Analyses will be repeated using different methods to verify the robustness of the results.Comparison of baselines – Mann‒Whitney U or independent sample T-tests: whether the groups will be comparable in terms of demographic characteristics and baseline scores. Chi-square tests will be used to compare categorical proportions between groups (if applicable).Analysis of the effect of the intervention: T-tests for dependent samples or Wilcoxon signed-rank tests will be used to compare pre- and postintervention values within the same group. ANCOVA (analysis of covariance): to control for confounding or baseline variables, ANCOVA could be useful. Mixed analysis of variance (ANOVA): for multiple repeated measures (for example, pre, post- and 3-month follow-up).Cluster analysis (if applicable): Multilevel analysis or mixed models. These models will be useful for considering the hierarchical nature of clusters in the data.Lost data management – sensitivity analysis: To determine if missing data affects the results. Imputation techniques such as multiple imputation could be used if there is a significant amount of missing data.

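### The protocol disagrees with itself on whether controls sit the immediate post-test; on the detailed schedule the intervention arm reaches month 3 with one more sitting of the same test, and the immediate arm contrast has no control data

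*Protocol article*

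**What the plan says.** The protocol article describes the control arm's testing in three places.

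- **Abstract, Methods/design.** The schedule is that "a knowledge test will be administered before and after the intervention and 3 months after the intervention". It then adds: "This test will also be carried out on the same time sequence in the control groups". Read plainly, controls sit the test three times.
- **Methods.** The intervention arm's pretest is "repeated immediately after the intervention and then 3 months later". For controls: "In the control groups, the test will be administered at the beginning of the study and repeated after 3 months". That is two sittings. Later in the same paragraph comes "This test will also be carried out at the same time in control groups with the same sociodemographic characteristics". This last sentence is ambiguous: it can mean all three times, or only that the shared tests are contemporaneous.
- **Data collection and sources of information.** After the game the intervention arm repeats the knowledge test and completes a satisfaction survey. Then: "The control group will not complete these post-intervention questionnaires". Both arms repeat the test after 3 months.

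Under Planned analysis, the mixed ANOVA is listed "for multiple repeated measures (for example, pre, post- and 3-month follow-up"). The same list includes paired within-group tests, ANCOVA and multilevel or mixed models.

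**The concern.** Two schedules are stated and sites cannot follow both. The choice between them changes what the knowledge data can show.

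If controls skip the immediate test, the arms differ at month 3 in two respects: one has played the game, and the same one has sat the test an extra time. Month 3 is the only time after baseline when both arms are tested, so the only randomised knowledge contrast carries that difference. The extra sitting coincides exactly with arm, so covariate adjustment or a multilevel model cannot separate it from the game. If re-sitting a test raises later scores, the bias favours the intervention.

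The immediate gain, for its part, would have no randomised comparator.

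**Working it through.** **Step 1. Count sittings per arm.**

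| Source | Intervention | Control |
|---|---|---|
| Abstract | before, after, 3 months (3) | same sequence (3) |
| Methods, specific sentences | pre, immediate, 3 months (3) | start, 3 months (2) |
| Methods, later sentence | not restated | ambiguous |
| Data collection | baseline, immediate, 3 months (3) | baseline, 3 months (2) |

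On the Data collection schedule, sittings before the month-3 test are 2 (intervention) and 1 (control), a difference of exactly one. On the abstract's schedule the difference is zero.

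**Step 2. Is it the same test?** The Learning section describes one 25-question test and mentions no parallel form. The Data collection section speaks of that test being answered again and repeated. The section on independent variables defines the educational intervention as the video game, so the extra sitting is not declared part of it.

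**Step 3. Fill the arm-by-time cells of the example ANOVA.** Two arms by three times gives 6 cells. On the Data collection schedule 5 have data, and control at immediate post is empty. The arm contrast at that time, and so the full arm-by-time interaction, cannot be estimated. A classical ANOVA restricted to participants with all three measurements would contain no controls. A likelihood-based mixed model can use the five filled cells, and ANCOVA on the 3-month score with baseline as covariate needs only the four cells that both arms share.

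**Step 4. Illustrate the possible size.** The protocol states no retest gain, so g below is an assumption. It means the gain still present at month 3 from one extra sitting.

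Inputs from the section on sample size: SD 4.07, planning effect 2.07, 131 per group, 20% loss, design effect 2.

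The stated 131 does not reproduce with the two-sided two-sample formula: 2 × (4.07 × (1.960 + 0.842) / 2.07)² = 60.7, so 61; × 2 = 122; / 0.8 = 152.5, so 153 per arm. That is a separate matter. The planned 131 is used here as it stands.

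- Effective n per arm = 131 × 0.8 / 2 = 52.4
- Non-centrality = g / 4.07 × √(52.4 / 2)
- Two-sided rejection at 5% with no game effect = Φ(−1.96 + ncp) + Φ(−1.96 − ncp)

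| Assumed g (points of 25) | g / 2.07 | ncp | Rejection, two-sided | Of which favouring the game |
|---|---|---|---|---|
| 0 | 0% | 0 | 5% | 2.5% |
| 0.25 | 12% | 0.314 | 6% | 5% |
| 0.5 | 24% | 0.629 | 10% (9.6%) | 9% |
| 1.0 | 48% | 1.258 | 24% (24.2%) | 24% |

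**The case against.** The strongest defence is that the working schedule is clear. The two places that describe control testing specifically agree on two sittings, and the plain outlier is one sentence in an abstract. The later Methods sentence can be read as consistent with them. This stands as far as it goes: the conflict lies between the abstract and the detailed text, and Methods need not be read as flatly contradicting itself.

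A reader might infer that the planned repeated-measures analysis cannot be run at all, or that the knowledge comparison is lost. The document does not support that. The three-time ANOVA is given only as an example, beside ANCOVA and mixed models, and the protocol does not commit to complete cases. Only the arm contrast at the immediate post-test is lost.

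A reader might also infer that a positive 3-month result would be shown to come from retesting, or that the false-positive rate is 10% to 24%. That is not supported either. Nothing in the document gives a retest gain, nothing says participants receive answers after the test, and the gain that matters is what remains three months later. It could be close to zero.

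Finally, the clinical-behaviour outcomes are not scored on this test, so the illustration does not apply to them. Collecting satisfaction only in the intervention arm is appropriate.

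What survives is that test exposure is unequal on the detailed schedule, that no listed method removes the inequality, and that the abstract describes a different design.

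**Conclusion.** The point holds as an inconsistency in the schedule together with a plausible bias of unknown size in the 3-month knowledge contrast. The contradiction and the one extra sitting follow directly from the text. The direction of bias rests on the assumption that re-sitting the test helps. The figures also assume a lasting gain between 0 and 1.0 points, the pilot's pre-post SD and the planned numbers; they show sensitivity and are not an estimate. The randomised 3-month comparison remains analysable, with this qualification. This should be fixed, but it does not invalidate the trial.

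**What to change.** Make the abstract, Methods and Data collection sections state one schedule.

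**Preferred.** Give controls the same online knowledge test, without the satisfaction survey, at a defined second time point matched to the intervention arm's post-test. Controls have no activity of their own, so that time point must be specified. Take the baseline-adjusted 3-month between-arm contrast as the main knowledge analysis. Both arms then have three sittings, and all six cells of the example ANOVA are filled. The cost is one more 25-question online test for about 131 controls, plus some extra prompting on the subject in an arm meant to receive nothing. This route closes once the matched time has passed, because a skipped test cannot be recovered.

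**If controls stay at two sittings.** Correct the abstract and clarify the later sentence in Methods. Limit the between-arm knowledge analysis to baseline and 3 months. Report the immediate gain as an uncontrolled within-group change, and state the extra sitting as a limitation of the 3-month contrast. This needs only changes of wording and no new data, but it discloses the unequal exposure without removing it.
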